### Sample size

The primary outcome of the study is cure rate at 12 weeks (in Chhattisgarh) or 16 weeks (in Telangana, Madhya Pradesh and Odisha) compared to the comparison area. Evidence on CMAM interventions in India testing its efficacy have shown cure rates ranging from 46.7 to 57.4% [19–23]. Another study from India found cure rate among 25–30% children with minimal community based interventions [26]. Hence for the sample size calculation, we therefore chose the expected cure rate with the proposed CSAM interventions of 50% and expected cure rate with existing government nutritional interventions of 25% to estimate the effect size of 25% (50–25%). The sample in each state will comprise of an equal proportion of children from the two age groups (6–23 months and 24–59 months). Using the significance level of 5%, with 80% power to detect the effect size of 25%, a design effect of 1.5 and accounting for 20% attrition due to loss of follow up and mortality, the sample size calculated for each age group of children is 100. Hence, the proposed sample size for the two age-groups of children in each state is 200 children. In total, the study will enroll 1000 children in all the five study states.

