### Intervention strategy

In general, the State Governments of Telangana, Madhya Pradesh, Odisha and Chhattisgarh will implement community-based management of SAM (CSAM) programme adapted from the WHO guidelines, in addition to the existing government nutrition promotion interventions. The approach will incorporate active and/or passive case-finding and screening for severe wasting by government frontline nutrition and health workers. For uniformity, children with WHZ < -3 will be categorized as experiencing SAM. SAM children will further undergo medical examinations and appetite test to identify complicated and uncomplicated cases. All complicated cases will be referred to the nearest nutritional rehabilitation centres (NRCs) for in-patient management. All uncomplicated cases will be enrolled in the CSAM programme for their community-based management in *anganwadi centres*. While the program’s primary focus is on treatment of children who are severely wasted, key activities also include regular follow up of all enrolled children at the *anganwadi centers*, counseling of caregivers on infant and young child feeding (IYCF), safe water, sanitation and hygiene practices, family planning and child care practices, promotion of vaccinations, appropriate referrals of sick children to NRCs or public health facilities and post discharge follow up. SAM children enrolled in the programme will also be given locally produced nutrient dense food supplements, antibiotics, anthelminthic and micronutrient supplements. Key aspects of the state specific CSAM programme are presented in Table 1. Detailed description of the state specific CSAM protocols and nutritional content of each locally produced nutrient dense food supplement is provided in Additional file 1. In the comparison area, where no CSAM intervention is being implemented, SAM children identified and enrolled in the study will receive the existing government nutrition promotion interventions. The existing program includes provision of double quantity of Take Home Ration (THR)^1^ for severely underweight children (which covers most of SAM children) and identification and referral of SAM children to Malnutrition Treatment Centres (MTCs).

**Table 1 Tab1:** Key aspects of the CSAM protocol that vary per state assessed

States	Screening & Identification	Admission criteria	Maximum treatment duration	Discharge criteria	Nutrient dense food	Post-discharge Follow up

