### Data collection, cleaning and storage

In the intervention states, the children enrolled in the study will be managed according to the state specific CSAM guidelines and locally produced nutrient dense food supplements. The study will assess the effectiveness of the CSAM programmes in terms of recovery of these children compared to the comparison arm. This will be assessed using anthropometric (length/height and weight) measurements and skinfold thickness (triceps and sub-scapular) to be taken on admission, at sixth week and at discharge by the trained field investigator. For anthropometric measurements, a digital weighing machine with a sensitivity of 10 g to measure weight and a wooden infant-cum-stadiometer to measure length/ height will be used. Length and height will be measured to the nearest 0.1 cm, weight to the nearest 0.01 kg and skinfold thickness to the nearest 0.1 cm. Weighing equipment will be calibrated using standard calibration weights and infant-cum-stadiometer will be calibrated with calibration rods. The skinfold caliper will also be calibrated daily. Before doing the data collection work, all Field Investigators will be trained and also complete anthropometric standardization exercises where their anthropometric measurement skills will be assessed for thoroughness, accuracy and precision. To assess the accuracy and precision of each Field Investigator, their measures will be compared to those of the master trainers, who will be considered the gold standard. Intra-observer technical error of measurement (TEM) and reliability will be calculated using the difference between the two measures of the Field Investigators. Inter-observer TEM and reliability will be calculated by comparing the Field Investigators two measures to the trainer’s measure [27].

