Also, during admission and at discharge, the Field Investigator will administer the questionnaire for capturing child details and incidences of morbidity. Additionally, during admission, data on availability of drinking and sanitation facilities and other household level socio-economic information will be collected. Also,24-h dietary recall, food frequency and food consumption questionnaires will be administered to these children on admission, at sixth week and at discharge to study food consumed by the children, food frequency and compliance of locally produced nutrient dense food supplements provided to the children as part of the intervention. Futhermore, we will also ascertain cause of death of any enrolled child died during the study period.

Besides, first 100 enrolled children in that state who qualifies for body composition measurement i.e. weight on admission > 5 kg, will also be measured for body composition parameters using BIA machine (InBody S10) on admission and at discharge.

Post discharge, the children will be followed up on a monthly basis for anthropometry until 6 months by the field investigators. Additionally, skinfold thickness and body composition assessment of all children will also be repeated at sixth month post discharge. A detailed description of data collection process is shown in Table 2.

**Table 2 Tab2:** Overview of all measurements that will be taken from children

Parameters	Method	Admission/ Baseline	6th Week	12th/16thweek/Exit/Discharge	Post-discharge Follow up^b^
All children enrolled:					
Child details, and history of illness	Questionnaire	**✓**		**✓**	
Drinking water and sanitation facilities and other household socio-economic status		**✓**			
Weight, Recumbent length/ Height,	Digital weighing machine, Infantometer/ Stadiometer	**✓**	**✓**	**✓**	✓
Skinfold Thickness (triceps & subscapular skinfold)	Holtain Skinfold Caliper	**✓**	**✓**	**✓**	✓^c^
Dietary assessment (24-h dietary recall & food frequency) and Consumption of locally produced nutrient dense food	Observation and questionnaire	**✓**^**a**^	**✓**	**✓**	
Body composition; For enrolled sub-sample of children (weight > 5 kg)					
Body fat mass	BIA machine	✓		✓	
Body lean mass					✓^c^

^a^At baseline only the 24-h dietary recall & food frequency assessment will be done

^b^Post discharge, all children will be prospectively followed up for anthropometric measurements on a monthly basis till 6 months by the field investigators

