### Data analysis

Final analysis will include all children enrolled in the study. Appropriate quantitative analyses will be used including descriptive statistics (proportion, percentage, mean or median), comparison of difference in proportion for binary outcome using Pearson chi-square and comparison of average change for continuous variable using t-tests. Recovery will be compared for effectiveness of state specific CSAM protocols and locally produced nutrient dense food supplements in four intervention states in comparison to the comparison state. Cox regression method will also be used for this analysis by defining recovery as event, as it can utilize the entire sample size including defaulters or loss to follow up. Other parameters including skinfold, defaulting, death, length of stay, average weekly weight gain and height gain will also be compared between the intervention states and the control state. Subgroup analysis will be done for comparing recovery among children aged 6–23 months and 24–59 months between intervention states and control state. For the sub-sample of body composition, change in fat mass, fat free mass and body water will be compared between the four intervention states and the comparison state. A linear mixed model will be developed for different outcomes (recovery, weight gain, and body composition parameters) adjusting for various random and fixed effects across all sites adjusted for differences at baseline.

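### The primary cure-rate weeks for Chhattisgarh and Madhya Pradesh are the reverse of their treatment durations in Table 1

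*Protocol article*

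**What the plan says.** The Sample size section of the protocol article gives the primary outcome as "cure rate at 12 weeks (in Chhattisgarh) or 16 weeks (in Telangana, Madhya Pradesh and Odisha) compared to the comparison area".

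Table 1, under Intervention strategy, has a column headed "Maximum treatment duration". It gives 16 weeks for Telangana, 12 for Madhya Pradesh, 16 for Chhattisgarh and 16 for Odisha. The discharge criterion is the same in all four rows: WHZ of at least -2, which is also how the Abstract defines cure.

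Under Data collection, cleaning and storage, enrolled children in the intervention states "will be managed according to the state specific CSAM guidelines". Their anthropometric measurements are "to be taken on admission, at sixth week and at discharge by the trained field investigator". Table 2 in that section heads the end-of-treatment column "12th/16thweek/Exit/Discharge" and does not say which state goes with which week.

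**The concern.** The sentence in the Sample size section is where the article sets the week of the primary outcome. For two states that week is the reverse of the treatment limit in Table 1. Taken literally, the sentence reads Chhattisgarh four weeks before its treatment limit and Madhya Pradesh four weeks after its own. The article gives no reason for either.

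The primary research question compares the four state programmes with the comparison state, and the Data analysis section plans a chi-square comparison of proportions. A cure proportion depends on when cure is counted. As written, an analyst could defend either week in two of the four contrasts. The article is also meant to inform states about their treatment protocols, so an error in Table 1 would misdescribe two of the programmes under evaluation.

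**Working it through.** **1. The two lists side by side.**

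| State | Week of primary cure rate (Sample size) | Treatment limit (Table 1) | Difference |
|---|---|---|---|
| Telangana | 16 | 16 | 0 |
| Odisha | 16 | 16 | 0 |
| Chhattisgarh | 12 | 16 | -4 |
| Madhya Pradesh | 16 | 12 | +4 |

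Both lists contain one 12-week state and three 16-week states. They differ only in which state has 12 weeks, which is the pattern of a clerical swap.

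**2. Is Table 1 merely broken in extraction?** No. In each row the duration stands between that state's own admission and discharge criteria and is followed by that state's own food product. The rows are intact.

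**3. Must the two lists agree?** One is an outcome week and the other a treatment limit, so they could differ in principle. The article links them in three ways. Children are treated under the state guidelines. They are measured at discharge. Table 2 puts the 12th or 16th week and exit or discharge in one column heading. On that reading the outcome week is the latest programme exit.

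**4. How many children?** Two states × 200 = 400, which is 400 of 4 × 200 = 800 intervention children and 400 of the 1000 in the study. This is the number in the affected states. Discharge occurs on reaching WHZ of at least -2, and that is also the cure definition. A child who reaches it and is discharged by week 12 counts as cured under either week. Only children still uncured at week 12 can change status. The documents do not say how many that will be.

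**5. Does the sample size depend on the week?** Inputs from the Sample size section: 50% against 25%, 5% significance (taken as two-sided), 80% power, design effect 1.5, attrition 20%. With the unpooled normal approximation:

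- n = (1.960 + 0.8416)² × (0.50 × 0.50 + 0.25 × 0.75) / 0.25² = 7.849 × 0.4375 / 0.0625 = 54.9, rounded up to 55
- 55 × 1.5 = 82.5
- 82.5 × 1.2 = 99 (dividing by 0.8 instead gives 103.1, so 104)

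The article states 100 per age group, so its figure is reproduced to within rounding. No week appears in the formula, and correcting the swap leaves 100 per age group and 200 per state as they are.

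**The case against.** The best case for the plan is that the harm is on paper. Field staff do not work from the sample size sentence. They follow the state guidelines and measure at discharge, so children would probably be measured at the true programme exit whichever list is wrong. Additional file 1, which is not shown, holds the state protocols and may settle the matter. The Data analysis section adds that "Cox regression method will also be used for this analysis by defining recovery as event", and a time-to-event analysis leans less on a single cut-off week.

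Much of this stands, and it limits the consequence. It does not remove the contradiction. Additional file 1 can show which place is right but cannot make both right. The Cox analysis is planned alongside the comparison of proportions and does not fix its week.

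Three stronger readings are tempting, and the documents support none of them.

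- *All 400 children are shifted by four weeks.* They are not, because early recoverers leave early (step 4 above).
- *The swap lowers the Chhattisgarh cure rate by a known amount.* The documents give no cure curve. Suppose Table 1 is right, cure is cumulative and 50% holds at week 16. A constant cure rate then gives 1 - 0.50^(12/16) = 40.5% at week 12, a drop of 9.5 points. A front-loaded curve (Weibull shape 0.5) gives 45.1%, a drop of 4.9 points. If no child is first cured in weeks 13 to 16, the drop is 0. These are assumed examples, not bounds. For Madhya Pradesh even the direction is open, since children may improve or fall back after treatment ends.
- *The comparison state is read at a mismatched week.* In that area, "where no CSAM intervention is being implemented, SAM children identified and enrolled in the study will receive the existing government nutrition promotion interventions", and it has no row in Table 1. The article leaves its week open but does not set a wrong one, and the Table 2 heading can cover both weeks. An article may leave that detail to the full protocol.

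**Conclusion.** The contradiction is certain and in the current text. The week of the primary endpoint conflicts for two of the four intervention-versus-comparison contrasts, by four weeks each and in opposite directions. The two states hold half of the planned intervention children, of whom only those not cured and discharged by week 12 could be affected. The sample size is unaffected, and no bias in the cure rates can be stated from the documents.

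This rests on two readings. The first is that the outcome week is meant to be the end of treatment, as the Table 2 heading indicates. The second is that cure is counted as attained at discharge, with later relapse a separate secondary outcome, as the Abstract lists it. Which of the two places is wrong cannot be decided from the article. The error probably arose as a clerical swap, but because the sentence defines the primary outcome it should be corrected.

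**What to change.** Check the Sample size section and Table 1 against the Madhya Pradesh and Chhattisgarh programme guidelines, and correct whichever is wrong.

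- If Table 1 is right, exchange the two state names in the Sample size sentence, so that Madhya Pradesh stands at 12 weeks and Telangana, Chhattisgarh and Odisha at 16. Leave the rest of the sentence unchanged. In particular, keep cure rate *at* the stated week: changing it to *by* that week would be a separate decision about the outcome definition.
- If the Sample size sentence is right, exchange the two durations in Table 1.

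The cost is a text correction, with no change to the sample size, the visits or the planned tests. It should be settled before the outcome data are analysed, so that the choice of week cannot follow the results.

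As a side note only, each contrast should use the comparison-area cure rate at the same week as the intervention state it is set against.

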### Selection of anganwadi centres

In each participating state, 100 *anganwadi centres* from the two study Blocks will be selected using probability proportion to size (PPS) sampling technique.

### Selection of study samples

In each of the CSAM intervention states, 200 SAM children aged 6–59 months identified using WHZ < -3, who will be enrolled in the CSAM programme and who do not have any medical complication and pass the appetite test will be enrolled in the study. Similarly, in the comparison state, 200 SAM children aged 6–59 months will be identified using WHZ < -3 by the Field Investigators and enrolled in the study, who do not have any medical complication and pass the appetite test. Children identified between October’ 2020 and December’ 2020 will be enrolled in the study.

We will exclude SAM children with presence of emergency signs, edema, high fever, cough with fast breathing and known secondary SAM cases like neurological diseases such as cerebral palsy, TB, HIV congenital heart defects, congenital structural defects and cleft palate. However, if any child enrolled in the study develops any medical complication later during the course of the study, s/he will be referred to inpatient care but continued to be part of the study.

The sub-set of children (first 50% of the enrolled children i.e. 100 children in each state) with weight at enrollment > 5 kg will be selected for body composition, as the BIA machine can only give accurate measurement for children with weight > 5 kg. So in total, 500 children will be selected for studying their body composition in the five study states.

For identifying eligible study participants in the CSAM intervention states, SAM children to be identified and enrolled by the frontline workers according to the identification criteria of the state specific CSAM programme from each of these selected *anganwadi centres*, will be rechecked by field investigators within 72 h and those children who will qualify on the basis of inclusion and exclusion criteria of the study, will be enrolled in the study. Similarly, in the comparison state, Field Investigators will identify eligible study participants and enroll in the study. Field Investigators will then approach caregivers of the children to explain the study and seek their written consent for participation. They will also be asked for permission to follow-up their children during the treatment phase and for 6 months’ post discharge in order to measure the impact of the interventions.

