**Methods:**

The longitudinal quasi-experimental study will be undertaken in two purposively selected blocks of one district each in the four intervention states and one comparison state. From each state, 200 SAM children identified using weight-for-length/height z-score (WHZ) < **−** 3 criteria will be enrolled in the study. Their anthropometric data and skinfold thickness will be taken on admission, at sixth week and at discharge by trained field investigators. Other child details, incidence of morbidity and socio-economic details will be collected on admission. To assess food consumption pattern including consumption of locally produced nutrient dense food supplements, dietary assessment, using 24-**h** dietary recall will be conducted on admission, at sixth week and at discharge. In addition, body composition parameters will be assessed for a sub-set of children using bio-electrical impedance analysis on admission and at discharge to analyse changes in total body water, fat-free mass, and fat mass. Post discharge, all study participants will be followed up monthly until 6 months. Atleast 10% of the sample will be checked for quality assessment.

The study’s primary outcome is cure rate defined as children attaining WHZ **≥** -2. Secondary outcomes include mean weight gain, mean length of stay, body composition parameters, relapse and mortality rates. Additionally, process evaluation and cost effectiveness analysis will be conducted.

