Telangana	Active screening- once in every quarter Passive screening on all MCH contacts	SAM identification by WHZ < -3SD	16 weeks	WHZ ≥ -2SD	Balamrutam+ under ICDS provision (composition- whole wheat, Bengal gram, roasted groundnut, Jaggery, vegetable oil and added vitamin & minerals) *477 Kcal and 11 g protein per 100 g*	Monthly follow up for 6 months
Madhya Pradesh	Active screening- once in every month Passive screening on VHSND/Health Sub-centre& all MCH contacts	SAM identification by WHZ < -3SD	12 weeks	WHZ ≥ −2SD	Take Home Ration (THR) under ICDS provision by MP Agro. State THR is a mix of cereals, pulses, oil, sugar, milk powder and soya bean. *440 Kcal and 17 g protein per 100 g*	Monthly follow up for 3 months
Chhattisgarh	Active screening- once in every quarter Passive screening on VHSND/Health Sub-centre& all MCH contacts	SAM identification by WHZ < -3SD	16 weeks	WHZ ≥ -2SD	ICDS based modified THR (wheat, soybean, chickpea, sugar, vegetable oil, groundnut, finger millet). *410 Kcal and 12.75 g protein per 100 g*	1st, 3^rd^and 6th month
Odisha	Active screening- once in every quarter Passive screening on VHSND/Health Sub-centre& all MCH contacts	SAM identification by WHZ < -3SD	16 weeks	WHZ ≥ -2SD	Augmented ICDS THR (additional oil, groundnut and whole milk powder). *462 Kcal and 16 g protein per 100 g* 1 egg daily in addition to THR	1st, 3rd and 6th month

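### As described, CSAM children qualify on two WHZ < -3 findings but comparison children on one identification with no recheck; this modestly dilutes each primary contrast

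*Protocol article*

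**What the plan says.** The Protocol article sets out two routes into the study under Selection of study samples.

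- **CSAM states.** The pool is "SAM children to be identified and enrolled by the frontline workers according to the identification criteria of the state specific CSAM programme". Table 1 (Intervention strategy) gives the same admission criterion for all four programmes: "SAM identification by WHZ < -3SD". Each such child "will be rechecked by field investigators within" 72 hours, and the study takes "those children who will qualify on the basis of inclusion and exclusion criteria of the study". Those criteria again include WHZ < -3.
- **Comparison state.** "200 SAM children aged 6–59 months will be identified using WHZ < -3 by the Field Investigators and enrolled in the study". The later paragraph on procedure says: "Similarly, in the comparison state, Field Investigators will identify eligible study participants and enroll in the study". No earlier screen and no repeat reading is described.

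The abstract (Methods) states that the "primary outcome is cure rate defined as children attaining WHZ" of -2 or more. Data analysis plans chi-square and Cox comparisons of recovery with no stated adjustment. It also plans a mixed model, with recovery among its outcomes, adjusted for baseline differences.

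**The concern.** Selection below a threshold on a noisy measurement admits some children whose true value lies above it. Asking for a second reading below the same threshold, by a different observer, removes many of them. If only the CSAM states apply the second reading, the comparison children are on average truly less wasted at entry than the CSAM children, even if the underlying populations are identical. They have less far to go to reach -2, so more of them reach it for the same true gain.

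All four primary contrasts use the same comparison state, so all four carry this component, and enrolling more children does not shrink it. It works against the programmes being evaluated, in a study meant to inform state policy.

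**Working it through.** **1. The planned effect.** Sample size assumes cure of 50% against 25%, 5% significance, 80% power, design effect 1.5 and 20% attrition, giving 100 per age group and 200 per state. With a two-sided test and unpooled variance:

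n = (1.960 + 0.842)² × (0.25×0.75 + 0.50×0.50) / 0.25² = 54.9, so 55. Then 55 × 1.5 × 1.2 = 99, which reproduces the stated 100. Dividing by 0.8 instead of multiplying by 1.2 gives 103.1.

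**2. WHZ distribution in the comparison district.** Study design and setting gives 29.0% below -2 and 10.7% below -3. A normal curve through both points has

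- SD = 1 / (1.243 - 0.553) = 1.45
- mean = -2 + 0.553 × 1.45 = -1.20

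**3. Assumptions not in the documents.** WHZ error SD of 0.1, 0.2 or 0.3 z for both readers, independent errors, and SD of true change 0.8 z. Mean change is set so that entry on one reading gives 25% cure (comparison) or 50% cure (CSAM).

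**4. Simulation (4 million children), one reading against two.**

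| Error SD (z) | 0.1 | 0.2 | 0.3 |
|---|---|---|---|
| One-reading cases also below -3 on the other reading | 93% | 87% | 80% |
| Mean true WHZ, one reading | -3.69 | -3.65 | -3.59 |
| Mean true WHZ, two readings | -3.74 | -3.75 | -3.75 |
| Comparison cure if two readings were used (25% with one) | 23.2% | 21.3% | 19.7% |
| CSAM cure under two readings (50% with one) | 47.9% | 45.7% | 43.7% |
| Difference, entry as written | 22.9 | 20.7 | 18.7 |
| Difference, two readings in every state | 24.7 | 24.4 | 24.0 |
| **Dilution due to the asymmetry (points)** | **1.8** | **3.7** | **5.3** |

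The last row is the row above it minus the one before, for example 24.7 - 22.9 = 1.8. Measured instead against the planned 25 points, the shortfall is 2.1, 4.3 and 6.3.

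**5. Power.** After attrition and design effect, 100 children count as 100 × 0.8 / 1.5 = 53.3, and 200 as 106.7. At 25% against 50%, power is 77% per age group and 97% per state. With the CSAM rates in the table it is 70, 61 and 53% per age group, and 94, 89 and 82% per state.

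**6. Effect of baseline adjustment.** Standardising cure to the field investigator's recorded admission WHZ, at the 25% level with equal true gain, leaves a gap of about 0.3, 1.1 and 2.2 points when weighted to the two-reading group. Weighted to the one-reading group it is 0.4, 1.4 and 2.8. The direction is unchanged. Some gap remains because a child's recorded value does not show whether a second reading would have confirmed it.

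**7. Robustness.** The direction was the same with noisier frontline readings, a smaller SD of change (0.5), a narrower population SD (1.1), and transient variation shared by both readings. At an error SD of 0.5 the shortfall against 25 points reaches about 10.

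**The case against.** **A single reading is inferred.** The article does not say that one reading suffices in the comparison state, and a field manual could require a repeat. That is fair, so the point is limited to what is described. It still stands, because the article spells out a recheck for one route and none for the other. The word that links the two routes does not supply a recheck, since its sentence names the field investigators alone as identifiers.

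**A reader might infer that the programme effect is hidden.** The figures do not support that. Over the assumed range most of the 25 points remain, and power per state stays at 82% or more. The lower figures per age group start from 77% before any dilution. Data analysis treats the age split as a subgroup analysis, although the sample size was set on it.

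**The size depends on an assumed error.** This stands. Data collection describes 10 g scales, length to 0.1 cm, calibration and standardisation exercises. These favour smaller error among field investigators but give no figure for it.

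**Adjustment is already planned.** This largely stands for the mixed model, which would remove more than half of the dilution over the assumed range. It does not help the chi-square and Cox comparisons, for which no adjustment is stated.

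**A reader might also infer that every contrast is biased towards no effect on balance.** That goes too far, because the districts differ. Using each district's own prevalences, equal true gains (mean 0.6, SD 0.9) and error SD of 0.15, 0.25 and 0.35, the net excess of comparison cure is 0.1, 1.4 and 2.6 points against Telangana and 0.5, 2.0 and 3.1 against Odisha. Within one population it is 2.0, 3.5 and 5.0. At SD 0.1 the net difference reverses slightly for these two states (-0.6 and -0.4). Only the component due to the entry rule has a settled direction.

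**Conclusion.** The concern holds as a dilution. The entry routes, as described, differ between the CSAM states and the comparison state, and that difference makes comparison children truly less wasted at entry, by about 0.05 to 0.16 z (3.74 - 3.69 and 3.75 - 3.59). The unadjusted cost is about 2 to 5 of the planned 25 points in each primary contrast. After adjustment for recorded baseline WHZ it is about 0.3 to 2 points, or nearer 3 at the upper end under the other weighting.

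These sizes rest on an assumed error SD of 0.1 to 0.3 z, independent errors, and a normal WHZ distribution fitted to the comparison district's two prevalences. Other differences between districts may enlarge or cancel the net effect. The problem is worth correcting because it is avoidable and cheap to remove, but it does not invalidate the study.

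**What to change.** - **Entry in the comparison state.** One field investigator screens. A field investigator blind to the first value takes a second reading within 72 hours. Enrol only children still below -3.
- **Baseline.** Use the field-investigator recheck reading as baseline WHZ in all five states, and keep both readings wherever they exist.
- **Recruitment already under way** (Trial timeline and status). Apply the rule to the remaining comparison enrolments and record for each child which entry rule was met.
- **Analysis.** Make the recovery comparison adjusted for baseline WHZ the main one. Add a sensitivity analysis that replaces the assumed error with the study's own technical error of measurement from the standardisation exercises. Those exercises cover field investigators, so the frontline error would still need a range.

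If a recheck is already done in the comparison state, a sentence saying so, with the rule used, settles the matter.

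**Cost.** One repeat weight and length/height per candidate in one state, by trained staff already on site, plus somewhat more screening: under the assumptions above, 7 to 20% of children first read below -3 would not be confirmed. Comparison children will also have entered under two rules, which the recorded flag lets the analysis examine.
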